### Randomization

Patients will be randomly assigned to either the intervention or the control group using a computer generated 4-block randomization scheme. The allocation will be performed by an independent person not otherwise involved in the study. The responsible researchers at each center request the group allocation by mail.

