## Background

The general prognosis for regaining ambulatory function after a traumatic SCI ranges from 3% in initially complete SCI patients (according to the Standard Classification of the American Spinal Injury Association ASIA A [1]) to 95% in very incomplete lesions (ASIA D) [2]. It is reported that for patients with a motor complete and sensory incomplete SCI (ASIA B) the chance to become ambulatory is 50%. Those subjects with preserved algesia seem to recover to about the same extent as motor incomplete SCI subjects [3].

The basis for locomotor training after acute spinal cord injury (SCI) in humans is provided by animal experiments which showed training induced plasticity of spinal locomotor centers [4]. In humans with a clinically complete spinal injury walking-like EMG activity can be elicited when subjects perform bodyweight supported and assisted stepping on a moving treadmill [5]. In SCI rehabilitation body weight supported treadmill training (BWSTT) has become established within the last 2 decades. In severely affected SCI subjects movements of the patient legs have to be manually assisted by two therapists. In some cases a third therapist might be needed to stabilize the pelvis. The shortcoming of such manual assisted BWSTT is that it is very exhaustive for the therapists and hence only allows for limited training time. In addition the application of movement assistance requires extra skills to maintain coordination between the two legs. In order to provide longer training sessions with a consistent movement pattern robotic gait devices were developed. These driven gait orthoses (DGO) become successively more established to treat individuals with a locomotor dysfunction such as incomplete SCI, stroke or traumatic brain injury [6]. A widely used DGO is the Lokomat (Hocoma AG, Volketswil, Switzerland, Figure 1) [7]. It has been shown that locomotor training with the Lokomat is feasible and that patients with a chronic incomplete SCI could improve gait speed and endurance as a response to an intensive training which lasted 8 weeks [8].

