## Methods/Design

The design of the study was developed in accordance with the Consolidated Standards of Reporting Trials (CONSORT statement)[16].

This study will take place at multiple sites (i.e. Zurich/CH (leading center), Barcelona/E, Toledo/E, Heidelberg/D, Murnau/D, Nijmegen/NL and Glasgow/GBR). Local Ethics Committees at each center have approved (Barcelona, Toledo and Zurich) the study. Informed consent will be obtained from all subjects prior to participation. Patients will be included as they are referred to one of the participating centers (consecutive sample).

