### Outcome

Outcome data will be assessed in the respective centers by therapists and medical doctors. Hereafter the data will be sent anonymously to the PI for analyses. Due to the characteristic of this study neither the therapists nor the assessors nor the patients can reliably be blinded regarding the group allocation. The principal investigator (PI) who is the first author of this report (MW) and will be involved in the analyses will not be aware of the respective intervention.

In order to describe the characteristics of the included subjects, demographic and clinical data will be assessed. The primary outcome is the self selected walking speed using the Ten Meter Walking Test (TMWT) [24]. It will be assessed at baseline, bi-weekly during training, and at the six months follow-up. In addition the following items will be assessed at baseline, bi-weekly during training, and after six months: the Walking index for spinal cord injury -WISCI [17] (an ordinal scaled index for the assessment of walking capabilities with 21 categories. Zero represents that the patient is not able to stand or walk, the maximum of 20 means that the patient can walk without bracing, walking aids or personal assistance), the maximum walking speed, the ASIA classification [1], the detailed Spinal Cord Independence Measure-SCIM [25], the modified Ashworth scale-MAS [26] of hip and knee joints, and the Penn spasm frequency scale [27]. During the training period the mechanical stiffness and the maximum voluntary torque of the legs as well as the cooperation of the patient during the training will be assessed bi-weekly using the force transducers of the robotic training device. For every training the distance walked, walking speed, walking time and body weight unloading, the rate of perceived exertion as well as the occurrence of any events (e.g. skin breakdown or joint stress or scheduling problems) will be assessed. At the end of the training period, i.e. after 8 weeks the patients subjective impression about the success of the training will be assessed using the Patients' Global Impression of Change Scale-PGIC [28].

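### A published block size of 4 in an unblinded trial leaves open whether sites can guess allocations, and ASIA grade is neither a named stratum nor a fixed covariate in the main comparison

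*Protocol article*

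**What the plan says.** The Randomization section gives the scheme in one sentence: "Patients will be randomly assigned to either the intervention or the control group using a computer generated 4-block randomization scheme". It adds that "The allocation will be performed by an independent person not otherwise involved in the study" and that "The responsible researchers at each center request the group allocation by mail". It names no stratum and does not say whether the list is central or by centre. The centres are "Zurich/CH (leading center), Barcelona/E, Toledo/E, Heidelberg/D, Murnau/D, Nijmegen/NL and Glasgow/GBR" (Methods/Design), and the same section says that "Patients will be included as they are referred to one of the participating centers (consecutive sample").

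The Outcome section says that "neither the therapists nor the assessors nor the patients can reliably be blinded regarding the group allocation".

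The Subjects section admits ASIA B and C and requires 23 patients per group. The Background gives chances of walking of 3% for ASIA A and 95% for ASIA D, and for ASIA B it says that "the chance to become ambulatory is 50" per cent. It gives no figure for C, and it notes that B patients with preserved pain sensation recover much like motor incomplete patients.

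The Analyses section makes the main comparison a two-group t-test or its non-parametric counterpart. ASIA grade and centre appear there only as possible confounders in multilevel models, to be used where required.

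**The concern.** There are two separate issues.

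**Guessable allocation.** An unblinded site sees every allocation it receives. If blocks of a known, fixed size run within a centre, the site can work out the end of each block. Someone who knows or suspects the next assignment can influence whether a patient is enrolled and when. There is room for that: several exclusion criteria call for judgement, and the start of training may fall anywhere up to day 60.

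**Prognostic imbalance.** The trial is small and enrols two ASIA grades. If grade is neither balanced by design nor fixed in the primary model, the arms can differ noticeably in grade by chance. The t-test then takes no account of it, and the choice whether to adjust can be made after the data are seen.

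**Working it through.** **Inputs from the protocol article.** 23 per group, 46 in total; difference 0.0418 m/s; SD 0.05 m/s; power 0.8; significance level 0.05; seven centres; 4-block scheme, read as block size 4.

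**The plan's own figure.** n per group = 2 × (0.05 × (1.96 + 0.84) / 0.0418)² = 22.46, rounded up to 23. The stated sample size is reproduced and is not affected by this point.

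**Guessing, if lists run by centre.** In a block of 4 with two patients per arm, the best guess at positions 1 to 4 is right with probability 1/2, 2/3, 2/3 and 1. The allocation is certain with probability 0, 0, 1/3 and 1.

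| Patients on the list | Guessed correctly | Certain in advance |
|---|---|---|
| 4 (complete block) | (1/2 + 2/3 + 2/3 + 1)/4 = 17/24 = 71% | (1/3 + 1)/4 = 33% |
| 6 | 4/6 = 67% | (4/3)/6 = 22% |
| 7 | 4.667/7 = 67% | (5/3)/7 = 24% |

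The expected number per centre is 46/7 = 6.6, so the last two rows are the realistic ones.

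**Guessing, if there is one central list.** This was simulated with blocks of 4, 46 patients falling at random on seven centres of equal expected size, and a guesser who sees only the centre's own history and picks the arm that is behind. The guess is right about 52% of the time.

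**Effect of varying the block size** (simulation; the guesser knows which sizes are in use):

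| Scheme | Certain, list of 7 | Guessed, list of 7 | Certain, list of 46 |
|---|---|---|---|
| Fixed 4 | 24% | 67% | 32% |
| Random 4/6 | 7% | 66% | 6% |
| Random 4/6/8 | 2% | 64% | 2% |

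Varying the blocks removes most certain allocations but hardly changes overall guessing.

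**ASIA imbalance without strata.** The share of ASIA B is not in the document; 30%, 40% and 50% are assumed, that is 14, 18 and 23 of 46. Under a hypergeometric distribution with 23 v 23, the SD of the difference in share is 14 to 15 percentage points. A gap of 20 points or more means at least 0.20 × 23 = 4.6, so 5 patients. Its probability is 11%, 13% and 24%. With an even number of B patients the gap must be even, so the first two figures are for 6 or more; this explains the jump to 24%.

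**Shift in the treatment contrast.** The B–C difference in walking speed is not given either, so it is an assumption. For a gap of 5 patients the shift is 5/23 × D:

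| Assumed D (m/s) | Shift (m/s) | Share of 0.0418 |
|---|---|---|
| 0.05 | 0.011 | 26% |
| 0.10 | 0.022 | 52% |
| 0.20 | 0.043 | 104% |

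**Consistency with the planned SD.** Two equal-sized grades whose means differ by D contribute an SD of D/2. For D = 0.10 that is 0.05 m/s, already the whole planned SD; for D = 0.20 it is 0.10 m/s, twice the planned SD. The upper end of the range therefore fits poorly with the plan's own variance.

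**The case against.** The document nowhere says that lists run by centre. One independent person answering requests from all centres fits a single central list at least as well, and then guessing is near chance. A condensed article may also leave the list structure and strata to the full protocol. A reader might infer that sites can decode the allocation, or that the trial decided against stratification; the text supports neither. Consecutive inclusion is a further safeguard. All of this stands, and the guessing concern is therefore conditional. What remains is that the block size is published, that the independent person cannot hide allocations a site has already seen, and that consecutive inclusion is only a partial safeguard.

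On ASIA grade, a reader might infer that unstratified allocation biases the result. It does not: randomisation without strata is valid, and chance imbalance is already reflected in the standard error. Nor does the Background show that B versus C is the main prognostic divide, given that it has no figure for C and likens some B patients to motor incomplete ones. The Analyses section also does provide for models with ASIA grade. These points stand too. But those models are optional and do not define the main test.

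**Conclusion.** The point holds in a limited form, as something that should be changed rather than an error that invalidates the design.

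- **Allocation.** The block size is fixed and public in an unblinded trial, and the article leaves the list structure open. The exposure ranges from negligible (about 52% guessed, one central list) to material (67% guessed, 22–24% certain, centre lists of 6 to 7 patients). The figures of 71% and one third apply only to complete blocks.
- **ASIA grade.** A gap of 20 points or more in ASIA B share would arise in 11% to 24% of trials, if 30% to 50% of patients are ASIA B. The consequence is lost precision and a single result that is harder to interpret. The shift in walking speed, 26% to 104% of the planned effect, rests wholly on an assumed B–C difference of 0.05 to 0.20 m/s, and no single value in it should be taken as an estimate.

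**What to change.** 1. State that one central list serves all centres and is held by the independent person. This matters most for guessing.
2. Use varying block sizes, for example 4 and 6, and do not disclose them to sites.
3. Preferably stratify the central list by ASIA grade (B or C) only. Do not cross it with centre: 2 × 7 = 14 strata would hold about 46/14 = 3.3 patients each, fewer than one block of 4.
4. Make ASIA grade a prespecified covariate in the primary analysis, in place of adjustment where required. The grade is already collected, so this costs nothing and can be done even if the list is left as it is.

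The cost of the first three changes is a new computer-generated list and one extra field on the allocation request. Incomplete blocks may leave the arm totals a few patients apart.

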### Intervention

The locomotor training with the Lokomat device should start within approximately 30 days but not later than 60 days after the SCI. The observation period of the training for this study lasts 8 weeks. For the initial 5 trainings there are no defined specifications. These trainings serve to optimize the setup and for the patients to familiarize with the robotic locomotor training device. During subsequent trainings following guideline will be adopted to adjust the training to the actual capacity: body weight unloading will be reduced to the least tolerated amount (no knee buckling or toe dragging). The walking speed will be set within the range of 1.6 to 3.1 km/h and the guidance force in the range from 100% (full assistance) to minimum tolerated. The training session will be shaped in the following way: 3 min walking without specification (warm-up period) after that, every 3^rd ^minute either speed, visual feedback or guidance force will be changed. This will avoid that the training becomes monotone and lacks challenge.

Patients who will be assigned to the intervention group receive one or two Lokomat trainings per day on 3-5 days per week. The Lokomat walking time per day should not be shorter than 50 min.

### Control

Patients of the control group receive one Lokomat training per day on 3-5 days per week. The Lokomat walking time per day should not be longer than 25 min.

### Outcome

Outcome data will be assessed in the respective centers by therapists and medical doctors. Hereafter the data will be sent anonymously to the PI for analyses. Due to the characteristic of this study neither the therapists nor the assessors nor the patients can reliably be blinded regarding the group allocation. The principal investigator (PI) who is the first author of this report (MW) and will be involved in the analyses will not be aware of the respective intervention.

In order to describe the characteristics of the included subjects, demographic and clinical data will be assessed. The primary outcome is the self selected walking speed using the Ten Meter Walking Test (TMWT) [24]. It will be assessed at baseline, bi-weekly during training, and at the six months follow-up. In addition the following items will be assessed at baseline, bi-weekly during training, and after six months: the Walking index for spinal cord injury -WISCI [17] (an ordinal scaled index for the assessment of walking capabilities with 21 categories. Zero represents that the patient is not able to stand or walk, the maximum of 20 means that the patient can walk without bracing, walking aids or personal assistance), the maximum walking speed, the ASIA classification [1], the detailed Spinal Cord Independence Measure-SCIM [25], the modified Ashworth scale-MAS [26] of hip and knee joints, and the Penn spasm frequency scale [27]. During the training period the mechanical stiffness and the maximum voluntary torque of the legs as well as the cooperation of the patient during the training will be assessed bi-weekly using the force transducers of the robotic training device. For every training the distance walked, walking speed, walking time and body weight unloading, the rate of perceived exertion as well as the occurrence of any events (e.g. skin breakdown or joint stress or scheduling problems) will be assessed. At the end of the training period, i.e. after 8 weeks the patients subjective impression about the success of the training will be assessed using the Patients' Global Impression of Change Scale-PGIC [28].

Since at the time of the study all patients will undergo a rehabilitation program, they receive along with the Lokomat training the usual rehabilitative therapy (i.e. physio and occupational therapy). In order to assure that the standard rehabilitation program is comparable between the participating centers, therapy schedules of one week will be collected of four patients per center. These schedules should contain the amount of therapy and roughly the content of the therapies (e.g. focus on arm or leg or standing and walking or other activities).

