### Analyses

All analyses will be performed in the leading center by the PI. He receives the data in form of an electronically completed case record form after completion of the training. For the analyses, the data will then be incorporated into the statistical software (PASW statistics 17.0, IBM-SPSS Inc. Chicago/IL).

In order to describe the characteristics of the sample, descriptive statistics will be applied. For the analysis of training induced differences between intervention and control group, T-Test for independent groups or the non-parametric correspondent depending on the outcome variable will be applied. In addition, multilevel models will be used to evaluate potential confounding factors (e.g. center effects, age differences, neurological level of lesion or ASIA) as required.

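### The analyst is said to be unaware of allocation, but the data flow as described would let the arm of any adherent patient be read from the recorded walking times

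*Protocol article*

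**What the plan says.** All statements are in the Methods/Design part of the protocol article.

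- **Who is not blinded (Outcome).** The article concedes that "neither the therapists nor the assessors nor the patients can reliably be blinded regarding the group allocation".
- **Who is (Outcome).** Of the PI it says: "will be involved in the analyses will not be aware of the respective intervention". This is the only masking that the article claims.
- **What is recorded (Outcome).** "For every training the distance walked, walking speed, walking time and body weight unloading" are assessed, together with perceived exertion and any events.
- **What the PI receives (Outcome, Analyses).** "Hereafter the data will be sent anonymously to the PI for analyses". Then: "He receives the data in form of an electronically completed case record form after completion of the training".
- **Who analyses (Analyses).** "All analyses will be performed in the leading center by the PI".
- **What defines the arms.** For control, "The Lokomat walking time per day should not be longer than 25 min", in one training per day. For intervention, "The Lokomat walking time per day should not be shorter than 50 min", in one or two trainings per day.

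The Intervention section adds that the first five trainings have no set specifications.

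**The concern.** The variable that separates the two arms is itself recorded at every training, and the one person described as unaware of the arm analyses all the data. Sending data anonymously removes the patient's identity but not the dose that the patient received. Replacing the group names by A and B does not help either, because anyone with the dose data can match the codes to the arms.

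What is at stake is analyst discretion. The article's main open choice is the multilevel models for confounders such as centre, age, lesion level and ASIA grade, which are to be used where needed. If the analyst can see the arms, decisions about whether to fit such a model and which covariates to include are made with knowledge of which result favours the longer training. Readers of the trial report would also credit a safeguard that may not have operated.

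**Working it through.** The blinding statement carries no figure to reproduce, and the planned 23 subjects per group do not depend on it. The check is whether the recorded data identify the arm.

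**Inputs**
- Control: at most 25 min/day, one training per day, 3 to 5 days per week (Control).
- Intervention: at least 50 min/day, one or two trainings per day, 3 to 5 days per week (Intervention).
- Training period 8 weeks, first five trainings unspecified, walking speed 1.6 to 3.1 km/h (Intervention).
- Assumptions: the patient adheres to the limits, and the five unspecified trainings fall within the 8 weeks.

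**1. Daily walking time.** 50 − 25 = 25 minutes. The permitted ranges are separated by a 25-minute gap and do not overlap, so one specified day identifies the arm.

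**2. Number of informative days.** Training days per patient: 3 × 8 = 24 to 5 × 8 = 40. The five unspecified trainings carry no arm information. At one training per day this leaves 24 − 5 = 19 to 40 − 5 = 35 days.

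**3. Two trainings on one day.** Walking time is logged per training, while the limits in the Intervention and Control sections apply per day. An intervention patient who trains twice for 25 minutes shows two entries equal to the control maximum. The daily sum still gives 2 × 25 = 50 minutes, and two trainings on one day are provided for in the intervention arm only. The Abstract words the limits per session; on that wording each single entry would separate the arms.

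**4. If entries could not be linked to days.** Total time over the specified days still separates patients who attend as planned. Control: at most 35 × 25 = 875 min. Intervention: at least 19 × 50 = 950 min.

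**5. Distance alone.** Distance is time multiplied by speed.
- Control, at most: 25/60 × 3.1 = 1.29 km/day.
- Intervention, at least: 50/60 × 1.6 = 1.33 km/day.

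The margin is narrow, but there is no overlap. Removing walking time while leaving distance in the file would therefore not restore the masking.

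**6. Does the analyst receive these records?** The article does not list the contents of the case record form. Three statements point to their inclusion. The per-training items are listed in the Outcome section, which also says that the data go to the PI. The PI performs all analyses. One stated aim, at the end of the Background, is whether training intensity is associated with adverse events, and that cannot be analysed without training data. No statement withholds or delays them.

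**The case against.** The strongest objection is that the contents of the form are inferred. The sentence on sending data to the PI follows directly on outcome data, and a condensed article may leave file layout and release order to a full protocol that is not shown. This stands as a limit on the wording: a reader might infer that the blinding has been shown not to exist, and the article does not establish that. It does not remove the point, because the article makes a positive claim of blinding and describes a data flow that, taken as written, defeats it.

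Other objections narrow the point:

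- **Every patient.** A reader might infer that all allocations are revealed on all 24 to 40 training days. The limits are worded as what should happen, so a markedly non-adherent patient could be ambiguous, and the first five trainings show nothing.
- **Choice of test.** A reader might infer that the analyst may freely choose between the t-test and its non-parametric counterpart. The Analyses section ties that choice to the outcome variable, so there is less discretion there than in the multilevel models.
- **Location of the PI.** That the analyses are done in the leading centre says nothing about awareness. No statement has the PI treat or assess patients or request their allocation.
- **Other safeguards.** Allocation is done by an independent person (Randomization), and the PI receives data only after training is complete, so cannot use them to steer that patient's training. Nor would analyst masking cure bias from unblinded assessors, which the article openly discloses. Both are correct, but neither keeps the analyst unaware of the arm.

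**Conclusion.** The concern holds in conditional form. If the PI receives the training records, which the article implies and nowhere excludes, the arm of any adherent patient is recoverable from daily walking time or from two trainings on one day. At one training per day about 19 to 35 days per patient carry that information, and one is enough. Group coding alone does not prevent it.

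This rests on three assumptions: that the case record form contains the per-training data, that the patient keeps to the daily limits, and that the five unspecified trainings lie within the 8 weeks. The consequence is confined to analyst discretion, chiefly the multilevel models, and to the credibility of the blinding statement. The size of any resulting bias cannot be computed from the article. Sample size, endpoint and planned test are unaffected.

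**What to change.** Split the data transfer and fix the order of release:

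1. Send the PI the baseline and outcome data with groups coded A and B.
2. Hold the training logs (walking time, distance, trainings per day, exertion, events) separately, for example with the independent person who performs the allocation.
3. Fix the primary analysis, including the rule for using multilevel models and their covariates, run it on the coded file and lock the result.
4. Only then release the training logs and the group labels.

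If this is not done, withdraw the statement that the analyst is unaware of the intervention and report the analysis as unblinded.

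The cost is two files instead of one and a lock date. The independent person is described as having no other part in the study, so keeping the logs would be a new task for that person or for another custodian. The feasibility and dose analyses must wait until the primary result is locked. Nothing changes in sample size, training or patient care.
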